### Recruitment strategy

Women visiting the antenatal clinic of the PBM hospital are being screened with the help of a one-page questionnaire to assess their eligibility for the study. We aim to screen around 6000 pregnant women from PBM hospital to reach the targeted sample size. The participants will have to satisfy the eligibility criteria (given below) before being recruited at baseline (figure 2) from February 2018 to March 2023:

**Figure 2 F2:**
[figure not shown]
Recruitment and follow-up strategy being used in GaRBH cohort.

10 weeks of gestation;Age: ≥18 to <35 years;Singleton pregnancy;Natural conception (ie, without any fertility treatment);No long-term medication (ie, not more than 2 weeks in last 1 year);No more than one miscarriage in previous pregnancies. In cases where the current pregnancy is the second pregnancy, then the women with miscarriage in their first pregnancy will also be excluded;No previous pregnancy affected by pre-eclampsia/eclampsia;No clinical evidence of sexually transmitted disease;No hormonal therapy.

We will not exclude the study participants (recruited in first trimester) who develop pregnancy complications in subsequent trimesters that may influence fetal growth (like pre-eclampsia,^72^ eclampsia, intrauterine growth restriction and gestational diabetes mellitus^73^). Exclusion of these complications in current pregnancy would lead to a reduction in the natural variation in the study population. Furthermore, we will not exclude preterm delivery cases due to its relationship with fetal growth^74^ and its high burden (ie, 12.8 million in 2010) in India,^75^ as it could lead to bias by restricting the sampling to very healthy pregnancies which may not represent the general population.

### Patient and public involvement

The fieldworkers are trained to establish rapport with the study population, which begins with describing the research questions and objectives of the study to the pregnant women visiting the antenatal clinic of PBM hospital during first trimester. Once they agree to consider participation, project staff discusses the participant information sheet, containing detailed information on all the measures and outcomes of the project with them in local language. Our data collection process starts only after taking the informed written consent from the eligible participants. We constantly try to involve them during the pregnancy by providing the readings of biochemical parameters and ultrasounds in each trimester and facilitate their antenatal visits in PBM hospital. The project staff will also provide support to the participant during and after the childbirth in the hospital. Moreover, the study population will be engaged through public events for the final dissemination of the study results.

## Assessment procedures and instrumentation

### Ultrasound measures

For ultrasound-based measurements relating to fetal growth, we are using the existing standard operating procedures described by INTERGROWTH study^76^ to ensure reliable data collection. The data are being collected by trained sonographers in Bikaner, who are highly familiar with the equipment (SonoACE R7 Samsung Healthcare) and experienced in conducting ultrasound examinations. The intraobserver variation will be assessed by repeat sonographic measurements on 10 participants on the same day. Comparisons will also be made between the readings of two sonographers of the hospital on 10 participants to assess interobserver variability. The interequipment variation in ultrasound measures will be assessed by comparing the PBM results of 10 participants with the radiology laboratory outside the hospital. We will measure the crown-rump length (CRL), biparietal diameter, occipitofrontal diameter, head circumference, femur length, anterior-posterior abdominal diameter. Gestational age based on CRL and fetal weight will be estimated with the help of INTERGROWTH equations.^76 77^

### Estimation of gestational age

The accurate estimation of individual-level gestational age during pregnancy is vital for interpreting fetal anatomy and growth patterns and predicting the date of delivery. Gestational age is being calculated from the first day of the last menstrual period (LMP). Moreover, for women providing clear information on LMP (in completed weeks and days) their gestational age is being confirmed with an ultrasound-based measurement of CRL in the first trimester, using an internationally recognised chart.^76^ If the difference between the CRL and LMP estimates is ≤7 days, LMP is being considered valid and taken as the true biological date.^76^ In women with an LMP and CRL difference of >7 days, CRL is being considered valid for estimating the gestational age.^78^

### Questionnaires

A comprehensive questionnaire has been developed for collecting information on demographic, anthropological (caste, religion and consanguinity), medical disease history, tobacco and alcohol intake and passive smoking. The validated food frequency questionnaire of '*Indian Migration Study'* is being used for evaluating dietary intake.^79^ Maternal physical activity during pregnancy is being assessed using the international physical activity questionnaire (ie, 7 days long).^80–82^ The assets-based tool of National Family Health Survey-4 is being used to evaluate socioeconomic position.^83^ For assessing depression, we are using the Patient Health Questionnaire^84^ and Edinburgh Postnatal Depression scale.^85^ The WHO-5 questionnaire is being used for collecting information on quality of life.^86^ The capability well-being, that is, individual’s freedom to function in five key areas of their life: ’stability', ’attachment', ’achievement', ’autonomy' and ’enjoyment', is being assessed by using the ICEpop CAPability measure for Adults.^87–89^ Information on maternal environment, gynaecological and obstetrics history is also being collected using tools adapted from INTERGROWTH study.^90 91^ Additionally, a structured questionnaire on social factors like relationships with family members, husband position in household, social support during pregnancy and travel is being used for assessing the quality of social life and adequacy of social support (table 1).

**Table 1 T1:** Measures, tools and time points of data collection

	Mother			Offspring
	First trimester	Second trimester	Third trimester	
Timing of data collection	10th to 13th weeks	22nd to 24th weeks	32nd to 34th weeks	Birth
Gynaecological and obstetric	✔	✔	✔	–
Socioeconomic position	✔	✔	✔	–
Anthropological (caste and religion)	✔	✔	✔	–
Education	✔	✔	✔	–
Marital status	✔	✔	✔	–
Smoking	✔	✔	✔	–
Alcohol drinking	✔	✔	✔	–
Medication	✔	✔	✔	–
Disease history	✔	✔	✔	–
Maternal environment	✔	✔	✔	–
Physical activity (IPAQ)	✔	✔	✔	–
Time-activity pattern	✔	✔	✔	–
Food frequency	✔	✔	✔	–
Dietary recall (3 days)	✔	✔	✔	–
PHQ-12	✔	✔	✔	–
Well-being (WHO-5)	✔	✔	✔	–
Depression (EPNDS)	✔	✔	✔	–
Social factors	✔	✔	✔	–
Capability well-being (ICECAP-A)	✔	✔	✔	–
Anthropometry				
Height/body length	✔	✔	✔	✔
Sitting height	✔	✔	✔	–
Weight	✔	✔	✔	✔
Circumferences	✔	✔	✔	✔
Skinfolds	✔	✔	✔	✔
Blood pressure	✔	✔	✔	–
Laboratory tests: Glucose, insulin, Hb, lipids, LFT and KFT and blood group	✔	✔	✔	✔
Metabolomic data	✔	✔	✔	✔
Ultrasound measures: CRL, BPD, OFD, HC, FL, AC and APAD	✔	✔	✔	–
Placenta and cord measures and images	–	–	–	✔
Body composition (DXA scan)	–	–	–	✔

APAD, anterior-posterior abdominal diameter; BPD, biparietal diameter; CRL, crown-rump length; EPNDS, Edinburgh Post Natal Depression Scale; FL, femur length; HC, head circumference; ICECAP-A, ICEpop CAPability measure for Adults; IPAQ, International Physical Activity Questionnaire; KFT, kidney function test; LFT, liver function test; OFD, occipitofrontal diameter; PHQ, Psychological health Questionnaire.

### Adult anthropometry

The assessment of anthropometric traits (weight, height, sitting height, circumferences and skinfolds) are being performed on study participants using standard procedures.^92^

Weight is being measured when the participant standing straight on the centre of the weighing machine (Tanita, model-HD380), arms hanging freely with minimum clothes and without accessories. Height is being measured as the vertical distance between vertex (highest point on head) and floor when the participant standing straight with feet together on the level floor without footwear, arms resting by the side, with head in eye-ear plane (Frankfort horizontal plane) and heels, buttocks and shoulders projected on the vertical plane using a wall-mounted stadiometer (ADE, Germany, model-MZ10023-3). Sitting height is being measured as the maximum distance from the vertex (top of the head) to the base of a flat sitting surface, with legs hanging freely and head in eye-ear plane.

Circumferences are being measured at the specific landmarks when the plane of the tape (ADE, model-MZ10021) is perpendicular to the long axis of the body and parallel to the floor without tape being pulled too loose or too tight. Waist circumference is being measured at the narrowest point (which is an approximate midpoint) around the waist between the lower rib margin of the last palpable rib and the top of the iliac crest with the help of a measuring tape. Mid-upper arm circumference is being measured at the midpoint between the tip of the shoulder and the tip of the elbow (acromion and olecranon process, respectively) taken horizontally (at the middle of the biceps). Hip circumference is being measured at the widest part of the hip (buttock) at the level of the trochanterion, which is the most superior point on the greater trochanter of the femur, not the most lateral point. Calf circumference is being measured on the right leg as the maximum circumference in a plane perpendicular to the long axis of the calf until the greatest circumference is located when foot is placed on raised platform.

Skinfold measurements are being taken in relaxing muscles by grasping a distinct fold that separates from underlying muscles with the help of Harpenden Skinfold calliper when the jaws of the calliper are perpendicular to the length of the fold on the site of measurement. Skinfold measurements at biceps, triceps, subscapular, suprailiac, medial calf and anterior thigh are being taken to the nearest 0.1 mm.

Three readings are being taken for all the anthropometric measures with minimum acceptable difference of 100 g, 5 mm, 5 mm and 2 mm between the readings for weight, height, circumferences and skinfolds, respectively. The readings are being recorded to the last completed grams or millimetre.

### Infant anthropometry

We will use the protocol of the International Fetal and Newborn Growth Consortium^93^ for measuring the infants. Birth weight will be taken within 30 min of delivery, without clothes and in stable condition when the infant is placed an electronic weighing scale (ADE, model-M114600) to the nearest 5 g. Infant length will be measured within 12 hours of birth using the baby length measuring board (ADE range 100–1000 mm), which has a fixed headboard and moveable footboard, placed on a raised flat platform on the level surface. The head of the infant will be positioned in eye-ear plane on the board and holding the infant’s legs with the left hand and moving the footboard with the right hand. Head circumference will be measured when the infant is on the lap of the field investigator, with stable head, using a measuring tape (SECA, 212) anchored just above the eyebrows on the forehead, and at the back the tape being positioned over the fullest protuberance of the skull. Three readings will be taken for all the newborn anthropometric traits with minimum acceptable difference of 10 g, 5 mm and 2 mm between the readings for weight, infant length and circumferences, respectively. The readings will be recorded to the last completed millimetre.

All the equipment used for the assessment of adult and infant anthropometric traits is being calibrated twice a week with the help of standard weights and measures.

### Blood pressure

Maternal blood pressure is being measured in the sitting position during each trimester after a rest of 5 min before taking the first reading, using an Omron blood pressure monitor (model: HBP-1300) validated for pregnant women^94^ and cuff of appropriate size. Three readings will be taken with 2 min interval between the readings with maximum acceptable difference of 5 mm Hg between two readings. The equipment used is being calibrated thrice a week with the readings of mercury sphygmomanometer.

### Biological sample collection and storage

A 15 mL of blood sample is being collected during each trimester from the study participants after overnight fasting (10 hours). We are using EDTA-coated, sodium fluoride-coated and plain tubes for blood collection for the separation of EDTA plasma, fluoride plasma and serum samples, respectively. Serum will be used for determining the levels of metabolites in addition to triglycerides, cholesterol, lipids, kidney function test (KFT), liver function tests (LFT) and insulin, whereas fluoride plasma will be used for measuring glucose levels. EDTA tube is centrifuged at 3500 rpm for separating the white blood cells (WBCs) (buffy coat), plasma and red blood cells. After separating the plasma, EDTA tube containing WBCs will be stored for future extraction of DNA for genetic and epigenetic studies. Multiple aliquots of serum and plasma collected at each trimester are being stored in a −80°C freezer (table 2).

We will collect cord blood and placenta at the time of delivery (table 2) and processed with the help of the standard operating procedure used in the '*Avon Longitudinal Study of Parents and Children'*, University of Bristol, UK. The cord blood will be collected in EDTA-coated, heparin-coated and plain tubes (10 mL each) and these will be processed for the separation of plasma and serum. The remaining sample in EDTA tube with buffy coat will be stored in a freezer at −80°C. In order to stabilise the gene expression, RNA*later* will be added in heparin tube. Placenta will be processed immediately after delivery and aliquots of tissue sample from maternal and fetal sides, cord tissue and membrane will be stored in a freezers at −80°C (table 2). All the stored aliquots will be appropriately bar-coded, stored independently in a separate storage box.

**Table 2 T2:** Type and number of aliquots of biological samples

	Pregnancy			Offspring
	First trimester	Second trimester	Third trimester	
Blood samples				
Serum	Six aliquots	Six aliquots	Six aliquots	–
EDTA plasma	Two aliquots	Two aliquots	Two aliquots	–
Fluoride plasma	Two aliquots	Two aliquots	Two aliquots	–
Buffy coat	One aliquot	One aliquot	One aliquot	–
Cord blood samples				
Serum	–	–	–	Four aliquots
EDTA plasma	–	–	–	Three aliquots
Heparin plasma	–	–	–	Three aliquots
Buffy coat with RNA*later*	–	–	–	One aliquot
Buffy coat	–	–	–	One aliquot
Placenta samples				
Maternal side tissue	–	–	–	Eight aliquots
Maternal side tissue with RNA*later*	–	–	–	Four aliquots
Fetal side tissue	–	–	–	One aliquot
Fetal side tissue with RNA*later*	–	–	–	One aliquot
Membrane tissue	–	–	–	One aliquot
Cord tissue	–	–	–	One aliquot
Cord tissue with RNA*later*	–	–	–	One aliquot

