### Laboratory tests

The fasting serum samples will be transferred to the Department of Anthropology, University of Delhi, on dry ice for the generation of data on biochemical assays on all the mothers during each trimester and also on their offspring using cord blood. The available auto-analyzer (XL-640, ERBA Mannheim, Czech Republic) in the Department of Anthropology, University of Delhi, India, will be used for biochemistry data generation (ie, glucose, insulin, lipids, KFT and LFT) after ensuring daily calibration. Insulin levels will be estimated using ELISA kits. Furthermore, a reagent lot calibration will also be performed whenever there is a change in lot number of the reagents to estimate the variation in assays between two reagent lots. For internal quality control, one blank per 100 samples and one control sample from *UK National External Quality Assessment Service* of known concentrations will be run in every 200 samples. Moreover, one duplicate and one sample of known concentration from the previous batch will be run per 100 samples for assessing intra-assay and inter-assay variation, respectively, to help with analyses in confirming repeatability and reproducibility of biochemistry data. Finally, 5% of the samples will be run in a different laboratory for all the biochemical assays as a measure of external quality control. Moreover, information on participant’s blood group, Sickle hemoglobin (HbS)and HIV infection, which are the part of standard protocol of the hospital’s antenatal care, will be taken from PBM Hospital.

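### The article disagrees with itself on the specimen for laboratory glucose, and schedules cord glucose without collecting any cord fluoride sample

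*Protocol article*

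**What the plan says.** Four places in the protocol article bear on the glucose specimen.

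- **Biological sample collection and storage, maternal paragraph.** "We are using EDTA-coated, sodium fluoride-coated and plain tubes for blood collection". Serum is to serve the metabolites, lipids, kidney and liver function tests and insulin, "whereas fluoride plasma will be used for measuring glucose levels".
- **Same section, cord-blood paragraph.** "The cord blood will be collected in EDTA-coated, heparin-coated and plain tubes (10 mL each"). Table 2 lists two fluoride-plasma aliquots per trimester for the mother and a dash for the offspring. Its cord-blood rows are serum, EDTA plasma, heparin plasma and two kinds of buffy coat.
- **Table 1 (under Questionnaires).** The row "Laboratory tests: Glucose, insulin, Hb, lipids, LFT and KFT and blood group" is ticked for all three trimesters and for the offspring at birth.
- **Laboratory tests.** "The fasting serum samples will be transferred to the Department of Anthropology, University of Delhi, on dry ice" for biochemistry on the mothers and "also on their offspring using cord blood". The auto-analyser "will be used for biochemistry data generation (ie, glucose, insulin, lipids, KFT and LFT) after ensuring daily calibration".

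No sentence says which cord specimen will serve for glucose.

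**The concern.** The maternal paragraph takes glucose out of the serum list and gives it a tube of its own. Fluoride is conventionally used for glucose because it slows the consumption of glucose by blood cells between collection and separation. The article does not spell out this reason, but its allocation of tubes matches it. Having made that choice, the plan schedules the same assay on cord blood and collects nothing there of the chosen type.

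At stake is the quality of one measured variable. If the mother's value comes from fluoride plasma and the newborn's from an uninhibited tube, a difference or association between them partly reflects specimen type. If all values come from serum, the types match but the protection chosen for glucose is given up throughout. Glucose also has some weight in this study: the Introduction repeatedly uses maternal glucose and hyperglycaemia to motivate work on fetal growth and newborn phenotype.

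**Working it through.** The article gives no figure for this point, so there is nothing to recompute. The check sets the statements side by side and follows each to its consequence.

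| Question | Mother | Newborn (cord blood) | Source |
|---|---|---|---|
| Is laboratory glucose planned? | Yes, each trimester | Yes, at birth | Table 1; Laboratory tests |
| Which tubes are drawn? | EDTA, fluoride, plain | EDTA, heparin, plain | Biological sample collection and storage |
| Are fluoride aliquots stored? | Two per trimester | None | Table 2 |
| Specimen named for glucose in the sample-collection section | Fluoride plasma | Not named | Biological sample collection and storage |
| Specimen named as shipped for the panel that includes glucose | Serum | Serum, if the opening sentence is read as covering both | Laboratory tests |

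**Step 1. Is there a gap for the newborn?** Yes. Glucose is scheduled on cord blood in two places, and neither the tube list nor the aliquot table provides "fluoride plasma" from cord blood. Cord glucose must therefore come from a specimen other than the one the plan assigns to glucose.

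**Step 2. Is the maternal specimen settled?** No. The sample-collection section says fluoride plasma. Laboratory tests mentions only serum as transferred for a panel that explicitly includes glucose.

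**Step 3. What follows under each reading?**

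- *The sample-collection section governs.* Maternal glucose is measured in fluoride plasma and cord glucose in serum, EDTA plasma or heparin plasma. The specimen types differ, and comparability is not assured.
- *Laboratory tests governs.* Both are measured in serum, so the types match. The inhibitor is then used for neither. The maternal fluoride aliquots, 2 × 3 trimesters = 6 per woman with complete follow-up, have no stated use.

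Neither reading leaves all four places consistent.

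**Step 4. How far does it reach?** The third objective relates the maternal metabolic profile to cord-blood metabolite levels. Those data come from the targeted kit described under Quantitative metabolomics. Metabolites are assigned to serum in the maternal paragraph, and Table 2 stores four cord-serum aliquots. That objective does not depend on a fluoride tube. What remains exposed is the laboratory glucose assay and any mother-offspring analysis that draws on it.

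**Step 5. Can a bias be sized?** No. The article gives neither a time from cord collection to separation nor a rate of glucose loss without fluoride.

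**The case against.** The strongest reply is that the fluoride sentence stands in the maternal paragraph and was never meant for cord blood, that the shipping sentence supports serum for both, and that cord handling follows the standard operating procedure of a UK birth cohort which is not reproduced. Time to centrifugation, temperature and separation would normally sit in that procedure, and their absence from a condensed article is no fault. With prompt separation the practical effect could be small. The data analysis section also names no mother-offspring comparison of laboratory glucose.

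Much of this stands, and it rules out several stronger readings that a reader might infer:

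- *That maternal and offspring glucose are not comparable.* This follows only if fluoride plasma is in fact used for the mothers. The article leaves that open.
- *That the third objective is compromised.* It rests on kit metabolites, with serum assigned for the mothers and cord serum stored.
- *That cord glucose will be low by some stated percentage, varying with the circumstances of delivery.* This needs a loss rate and a delay, neither of which is in the document, and it presumes uncontrolled handling that no sentence describes.
- *That cord glucose already collected should be left out of mother-offspring comparisons.* This would rest on that undemonstrated bias.

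The reply does not remove the contradiction. Condensation can explain missing detail, but here tubes and aliquots are itemised and the lists do not fit the assay schedule. An unseen handling procedure cannot supply a fluoride aliquot that Table 2 does not contain. The serum reading rescues comparability only by overriding the explicit assignment of glucose to fluoride plasma.

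**Conclusion.** The point holds as an internal contradiction with a limited but real consequence. Table 1, the sample-collection section with Table 2, and Laboratory tests do not agree on the specimen for laboratory glucose. Under one reading maternal and cord glucose differ in specimen type. Under the other, neither uses the inhibitor the plan selected. The reach is one assay in the biochemistry panel plus any analysis linking mother and newborn through it; the kit-based metabolite analyses are outside it.

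The conclusion assumes that the tube list and Table 2 are complete as printed, and that the glucose tick at birth in Table 1 is intended, which Laboratory tests supports. It makes no claim about the direction or size of error in cord glucose. The correction is still worth making because it is specific, inexpensive and removes an avoidable source of measurement error.

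**What to change.** Name one glucose specimen for mothers and newborns, and make Biological sample collection and storage, Table 2 and Laboratory tests all say so.

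- *If fluoride plasma is kept:* add a small fluoride tube filled from the cord blood already being collected, add a cord fluoride-plasma row to Table 2, and amend Laboratory tests so that glucose is assayed in fluoride plasma, not in the shipped serum.
- *If serum is chosen instead:* change the sentence that assigns glucose to fluoride plasma, acknowledge that no inhibitor is used, and state what the stored maternal fluoride aliquots are for.
- *For births sampled without a cord fluoride tube:* record the specimen type used and the time to separation, and report cord glucose with that limitation.

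Under the first option the cost is one extra low-cost tube per delivery, with its aliquot, plus text edits. No additional procedure on mother or newborn is needed. The second option costs text edits only, but gives up the protection the plan chose for glucose.
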